**Discussion:**

This study aims to provide high-quality evidence for the efficacy and safety of IA for treating RA. In addition, the results will provide references for selection of acupoints for other syndromes in clinical practice.

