## Methods/design

### Aim

The aim of this study will be to design a detailed research protocol for IA treatment for RA patients in China and to explore its clinical efficacy, adverse reactions, and safety.

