### Power calculation

Sample size was determined based on the formula for sample size calculation comparing two groups with independent sampling rates:
$$ \mathrm{n}1=\mathrm{n}2=\frac{{\left({Z}_{1-\alpha /2}+{Z}_{1-\beta}\right)}^2\left[{P}_1\left(1-{p}_1\right)+{P}_2\left(1-{p}_2\right)\right]}{{\left({p}_1-{p}_2\right)}^2} $$

Based on previous clinical research, the rate for the trial group that received IA for RA treatment was 95% and that of the control group was 78% [16]. In this study, assuming *α* = 0.05 (both sides) and 1 − *β* = 0.80, the required sample size was calculated as 60 per group. Considering a dropout rate of 10%, we concluded that the required sample size was 66 per group. Therefore, a total of 132 patients with RA will be recruited.

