### Data analysis

Data analysis will be performed using SPSS software (version 23.0; IBM SPSS Statistics, New York, USA) by statisticians independent of the research team.

Baseline data including age, sex, disease duration, evaluation of TCM syndromes, HAQ score, DAS28 score, and CRP values before interventions will be compared between the two groups. All analyses will be strictly conducted according to the intention-to-treat principle. Continuous variables such as age, disease course, and values of DAS28, HAQ, and CRP will be presented as mean ± standard deviation (SD). Categorical variables such as TCM syndromes will be presented as percentages. Student’s *t* tests will be used to compare quantitative data between the two groups. Data on adverse reactions will be analysed using the *X*^2^ test. Differences will be considered statistically significant at *P* < 0.05. Missing data will be imputed by multiple imputation. To assess the robustness of the results, a sensitivity analysis using a pattern-mixture model will be used.

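### Safety is a stated aim, but the only between-group analysis named for adverse reactions is a chi-square test at P < 0.05, which cannot show how large an excess of harm is ruled out

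*Protocol article*

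**What the plan says.** The Aim section sets out "to explore its clinical efficacy, adverse reactions, and safety". The abstract's Background and the last paragraph of the main Background also name safety. The abstract's Discussion goes further: "This study aims to provide high-quality evidence for the efficacy and safety of IA for treating RA".

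In the Data analysis section, harms get one sentence: "Data on adverse reactions will be analysed using the" chi-square test. The next sentence is a general threshold for all comparisons: "Differences will be considered statistically significant at" P < 0.05.

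The Power calculation section is built on efficacy: "the rate for the trial group that received IA for RA treatment was 95% and that of the control group was 78" per cent. With two-sided alpha of 0.05 and power of "0.80, the required sample size was calculated as 60 per group". Then: "Considering a dropout rate of 10%, we concluded that the required sample size was 66 per group". No adverse-reaction rate, and no difference in harm that would matter, enters the calculation or appears elsewhere in the article.

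Safety conduct is covered separately. The Patient safety section has pain, dizziness, pruritus and local redness recorded in the case report forms, and serious events reported at once. The Data management section provides an independent monitoring committee and a termination decision by the main investigators.

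**The concern.** A test of no difference answers one question: are the data hard to reconcile with equal adverse-reaction rates? A safety aim asks another: how much extra harm could real needles cause, compared with tape alone, and still fit these data? A P value does not answer the second question. When the result is significant, it does not say how large the excess is. When it is not, it does not say how large an excess remains possible.

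The choice matters here because the number of patients was fixed for a 17-point difference in efficacy (95% v 78%), and power for adverse reactions at that size was not considered. If the end-of-trial comparison of harms is reported only as a P value, the safety half of the question gets an answer from which no limit on harm can be read, while the abstract promises strong evidence on it.

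**Working it through.** **1. The plan's own figure.** Inputs from the Power calculation section: p1 = 0.95, p2 = 0.78, two-sided alpha 0.05, power 0.80. With the formula given there:

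n = (1.960 + 0.842)² × [0.95 × 0.05 + 0.78 × 0.22] / (0.95 − 0.78)²
= 7.849 × (0.0475 + 0.1716) / 0.0289 = 59.5, so 60 per group.

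Adding 10% gives 60 × 1.1 = 66. The stated figures reproduce, and every input is an efficacy quantity.

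**2. What the chi-square test can detect at that size.** The article gives no adverse-reaction rates, so the rates below are assumptions and a range is shown. Method: for every pair of counts (a, b) from 0 to n in the two arms, compute the uncorrected Pearson statistic

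X² = (a − b)² × 2n / [(a + b)(2n − a − b)],

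call it significant above 3.841, and sum the binomial probabilities of the pairs that are not significant.

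| Assumed rate, sham v IA | Missed, 66 per group | Missed, 60 per group |
|---|---|---|
| 1% v 5% | 76% | 80% |
| 2% v 6% | 80% | 82% |
| 2% v 8% | 65% | 69% |
| 2% v 10% | 49% | 54% |
| 5% v 10% | 81% | 83% |
| 5% v 15% | 50% | 54% |
| 10% v 20% | 64% | 67% |
| 5% v 20% | 23% | 27% |
| 10% v 30% | 16% | 20% |
| 5% v 25% | 8% | 10% |

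The 60-per-group column shows the position if only the pre-dropout number is analysed. A continuity-corrected test would miss more (66 per group: 5% v 10%, 90%; 5% v 15%, 63%).

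**3. What one non-significant table looks like.** Take 6/66 with IA and 1/66 with sham (9.1% v 1.5%).

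X² = (6 − 1)² × 132 / (7 × 125) = 3300 / 875 = 3.771, P = 0.052.

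The Newcombe interval uses the Wilson limits of each proportion: 4.2% to 18.4% for IA and 0.3% to 8.1% for sham. The risk difference is 7.6 points.

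Lower limit: 7.6 − √[(9.1 − 4.2)² + (8.1 − 1.5)²] = −0.6 points.
Upper limit: 7.6 + √[(18.4 − 9.1)² + (1.5 − 0.3)²] = +17.0 points.

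(The limits were computed from unrounded values.) The test says only that the difference is not significant. The interval says that an excess of up to 17 points has not been excluded.

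**4. What zero events would show.** With 0/66 in the IA arm, the exact upper bound on the true rate is 1 − 0.05^(1/66) = 4.4% (one-sided 95%), or 1 − 0.025^(1/66) = 5.4% (two-sided 95%).

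**The case against.** A reader might infer that the plan adopts a rule by which P above 0.05 counts as proof of safety. The text does not support that. The threshold sentence is general, says when a difference is called significant, and says nothing about what follows when it is not.

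A reader might also infer that the trial will probably overlook harm, even a several-fold increase. That does not follow either. The miss rates depend on assumed event rates, and the article does not define what excess would be clinically relevant. At 66 per group a four-fold rise from 5% to 20% is detected 77% of the time, and a three-fold rise from 10% to 30% is detected 84% of the time.

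Safety is not left to the chi-square test alone. Event recording, immediate reporting of serious events and an independent committee are all provided for. They govern the conduct of the trial, however, and give no end-of-trial comparison of rates. The Data analysis section also has categorical variables shown as percentages, which may well cover adverse reactions by arm.

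Finally, confidence intervals and incidence tables often sit in a full protocol or SAP, neither of which is shown, so their absence alone would not be a finding. Most efficacy-sized trials are weak on harms, and the stated aim is only to explore.

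These points narrow the concern but do not remove it. The article itself selects a difference test for harms, and itself promises high-grade evidence on safety. The two do not match.

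**Conclusion.** The point holds in a limited form. For a stated aim, the article fixes a between-group analysis that cannot by itself bound the excess of harm, in a trial sized on efficacy alone. A non-significant result would be weak evidence against a modest excess: under assumed rates, 50% to 81% of such results are missed for 5% v 10% to 15%, and 65% for 2% v 8%. It would be better evidence against a large excess (23% missed for 5% v 20%; 16% for 10% v 30%). These figures assume an uncorrected chi-square test, 66 analysed per group and one yes/no outcome per patient. They describe the test under those rates and do not predict this trial's result. This is a worthwhile correction to the analysis and wording, not a fault that threatens the trial.

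**What to change.** In the Data analysis section, make estimation the main safety analysis:

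- Report the number and proportion of patients with at least one adverse reaction in each arm.
- Report the risk difference, IA minus sham, with a 95% Newcombe confidence interval.
- Where no event is seen in an arm, give the exact upper bound for that arm's rate (for 0/66, 5.4% two-sided or 4.4% one-sided), and say which is used.
- Keep the chi-square P value as a supplement.
- State that the safety conclusion will be worded by the upper confidence limit (the excess above which harm is excluded) and not by non-significance.

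In the abstract's Discussion, soften the claim about safety to what 66 patients per arm can support.

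The cost is a few sentences and some table columns, from data already recorded in the case report forms. No extra patients or visits are needed. The small downside is a more modest safety claim.

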## Discussion

RA is a chronic autoimmune disease which presents with serious disability and dysfunction [5, 20]. RA affects 0.5% of adults worldwide and is two to three times more common in women than in men [21]. The incidence of RA in the USA and China is 0.5–1.0% [2] and 1.02%, respectively [22]. DAS28-CRP is widely used to monitor disease activity and is based on the number of swollen or tender joints, serum CRP, and global patient assessment [23, 24]. Pharmacotherapy is the first line of treatment for RA. The application of anti-rheumatic drugs at early diagnosis and treatment of RA improves joint swelling and tenderness and delays the process of joint destruction [25, 26]. Nevertheless, adverse side effects of drugs are common. Therefore, there has been growing interest in complementary and alternative medicine treatments for RA.

Acupuncture is an important component of TCM and is widely used in the treatment of patients with RA in China. Evidence suggests that acupuncture alone or in combination with other treatment modalities is beneficial for clinical treatment of RA, does not result in adverse effects, and significantly improves quality of life and function [5, 27]. Nevertheless, traditional acupuncture has drawbacks. For instance, patients may be apprehensive about undergoing continuous traditional acupuncture therapy due to time and manipulation factors. To address this, IA may be selected. Intradermal needles were developed using the ancient shallow needling method. These small needles are inserted into the subcutaneous tissue and are retained after fixation. This enables continuous stimulation of the body over a prolonged period, a state termed “embedding needles”, which combines the advantages of embedding thread and acupuncture. IA has the advantages of simple operation, lasting effects, low pain stimulation, and high compliance. It is particularly suitable for individuals who are apprehensive about acupuncture [28].

In this study, the inclusion criterion of age was set to above 18 years to ensure coverage of a wide age range. In addition, we will enrol RA patients with liver and kidney deficiency syndrome as research participants for third reasons. First, TCM nursing technology places substantial importance on the principle of “syndrome differentiation and treatment” via syndrome differentiation and acupoint selection. In this regard, the optimal therapeutic effects can be achieved and observed more objectively and comprehensively. Second, liver and kidney deficiency syndrome is a common syndrome observed in clinical practice [29]. Third, RA pathogenesis is underpinned by a deficiency in healthy qi and pathogenic factors. Treatment should therefore focus on eliminating pathogenic factors and strengthening healthy qi. Selecting patients with liver and kidney deficiency syndrome will help to strengthen the body and achieve better therapeutic effects.

A limitation of our trial is that IA operators will not be blinded to the nature of the intervention. To reduce confounding effects on patients, operators will be informed of patient group assignments just before treatment. The results of this trial will provide more reliable evidence and clarify the value of IA as a treatment for RA. Further, our study will provide a reference for selecting acupoints for other syndromes.

## Trial status

This trial was registered on 8 September 2020 at the Chinese Clinical Trial Registry (Registration number: ChiCTR2000038028, the protocol version number: 2.0, version date: 19 August 2020). This trial is currently in the stage of patient recruitment. The first patient was enrolled on 15 December 2020. Patient recruitment is expected to end on 30 March 2022.

## Data Availability

This trial does not involve the storage of biological specimens. The data and materials used during the current study are available from the corresponding author on reasonable request.

## Abbreviations

IA: Intradermal acupuncture
RA: Rheumatoid arthritis
TCM: Traditional Chinese medicine
ECG: Electrocardiogram
ARA: American Rheumatology Association
ACR: American College of Rheumatology
EULAR: European League Against Rheumatism
HAQ: Health Assessment Questionnaire
DAS28: Disease Activity Score 28
CRP: Serum C-reactive protein
GH: General health
SJC: 28 Joint swelling index
TJC: Joint tenderness count
ESR: Erythrocyte sedimentation rate
VAS: Visual analogue scale
CRFs: Case report forms
